### Randomization and allocation concealment

An independent statistician ([name]) will generate a random assignment code using the block randomization method in block sizes of 2 and 4 with no stratification in SAS® Version 9.4 (SAS Institute Inc., Cary, NC). Participants that satisfy the eligible criteria will be assigned to the HHT or placebo granule group at the baseline visit (Week 0), with a 1:1 allocation ratio. The generated code will be sealed in opaque envelopes and stored in double-locked cabinets. We will maintain allocation concealment throughout the study period by giving participants identically packaged, consecutively numbered drug containers.

### Blinding

The participants, investigators, outcome assessors, pharmacists, study monitors and data managers will be blinded to which medication will be administered to participants by using placebo granules as a control. The independent statistician who generated the random assignment code will provide the random assignment table directly to Hanpoong Pharm & Foods Co., Ltd. (Jeonju, Republic of Korea), and the company will pack and deliver investigational products to the hospital. The placebo granules will have the same formulation and properties as the HHT granules to prevent any bias in efficacy and safety assessments. Blinding will be maintained until all participants have completed the study, unless serious medical emergencies occur to participants. When unblinding is necessary such as in serious medical emergencies, a separate emergency code stored in double-locked cabinets will be opened by investigators. The investigators must document the reason for unblinding. To check whether the participant blinding is maintained during the study period, investigators will perform a blinding test on participants after 8 weeks of investigational product administration (Visit 4). Investigators will ask the participants which type of drug they think was administrated: “real drug,” “false drug,” or “do not know.” The success of blinding will be evaluated using the new blinding index and 95% confidence interval [21].

### Interventions

Eligible participants will be randomly assigned to receive HHT or placebo granules for 8 weeks. The HHT granule is made of an herbal extract, lactose hydrate, and corn starch. The herbal extract is composed of four herbs: *Coptidis Rhizoma*, *Phellodendri Cortex*, *Scutellariae Radix*, and *Gardeniae Fructus*. The raw materials (*Coptidis Rhizoma* 0.67 g, *Phellodendri Cortex* 1.0 g, *Scutellariae Radix* 1.0 g, *Gardeniae Fructus* 1.0 g) are extracted with 8 to 10 times the volume of water at 90–100 °C for 3–4 h. The extract is filtered and the filtrate is concentrated under reduced pressure at 60 °C or lower to obtain the herbal extract. The placebo granule is made of lactose hydrate, corn starch, hydroxypropyl methylcellulose, ginseng-flavored powder, and caramel coloring.

The HHT and placebo granules will be provided by Hanpoong Pharm & Foods Co., Ltd. (Jeonju, Republic of Korea) and are manufactured so that there is no difference between them in shape, color, smell, or taste. A blinded pharmacist will check the storage, dispensation, and quality of the investigational product.

Participants will be instructed to take one pack (3.0 g) at a time, three times per day for 8 weeks. The dosage regimen is based on authorization by the Korea Ministry of Food and Drug Safety. Participants will be instructed to return unopened packages of the investigational product to check their adherence to treatment. If any adverse events occur, investigators will take appropriate action depending on the severity of the adverse event and the causal relationship with the investigational product.

Co-administration of medications that are being used for the management of metabolic diseases, such as hypertension and diabetes, and dietary supplements that do not directly affect hyperlipidemia can be permitted during the study period. However, participants will be instructed not to change the dose or type of concomitant medications as much as possible and if they are changed, the investigators will record the details in the case report form (CRF).

Drugs that can cause dramatic changes in the gut microbiome (such as antibiotics and lactic acid bacteria) should be used cautiously only if needed, to minimize the effect on the gut microorganism, which is an exploratory outcome measure of this study. For participants who are already taking lactic acid bacteria, the investigators will instruct them not to change the dose or type as much as possible during the trial. If there is any change, the investigators will record the details in the CRF.

The use of statins, ezetimibe, fibric acid derivatives, PCSK9 inhibitors, cholestyramine, nicotinic acid, omega-3 fatty acids, systemic steroids, diuretics, amiodarone, and cyclosporine, which can affect the lipid profile, and the use of drugs that can affect thyroid function such as thyroxine will be forbidden during the study period. However, the use of 4 g omega-3 fatty acids or less per day and short-term use of 6 mg or less per day of dexamethasone or equivalent corticosteroids within 5 days, which would not affect lipid levels [19, 20], are allowed.

Dietary content and the physical activity level of participants are factors that may affect the results of this trial. In addition, gut microflora is affected by recent dietary intake. Therefore, we will compare food intake and the degree of physical activity before and after 8-weeks of investigational product administration by using a 3-day food record and the validated Korean version of international physical activity questionnaire short form [22], respectively. Participants in both groups will be educated and instructed to follow dietary and exercise guidelines for hyperlipidemia using a brochure based on the Korean Guidelines for the Management of Dyslipidemia [4].

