### Exclusion criteria

Having a history of unstable angina, myocardial infarction, transient ischemic attack, cerebrovascular disease, coronary artery bypass surgery, coronary intervention, or abdominal aneurysm within 3 months prior to screeningUse of statins, ezetimibe, fibric acid derivatives, proprotein convertase subtilisin/kexin type 9 (PCSK9) inhibitors, cholestyramine, nicotinic acid, omega-3 fatty acids, systemic steroids, diuretics, amiodarone, and cyclosporin, which can affect the lipid profile within 4 weeks prior to screening (however, the use of 4 g omega-3 fatty acids or less per day and short-term use of 6 mg or less per day of dexamethasone or equivalent corticosteroids within 5 days, which would not affect lipid levels, are allowed [19, 20])Uncontrolled hypertension with systolic blood pressure of more than 180 mmHg or diastolic blood pressure of more than 110 mmHgUncontrolled diabetes mellitus with HbA1c of more than 9% or fasting blood glucose of more than 160 mg/dlUncontrolled thyroid function (thyroid-stimulating hormone (TSH) levels ≥ 1.5 times the upper limit of normal)TG levels of more than 500 mg/dlSevere liver or renal disease (aspartate aminotransferase (AST) or alanine aminotransferase (ALT) levels ≥ 3 times the upper limit of normal or creatinine levels ≥ 2 times the upper limit of normal)Participants with a history of alcohol abuse or drug abuse within the past yearWomen who are pregnant or lactating, or women who do not agree to use effective methods of contraception during the clinical trialParticipants with genetic problems, such as galactose intolerance, Lapp lactase deficiency, or glucose-galactose malabsorptionParticipants with known hypersensitivity to the investigational productsParticipants who had taken other investigational products within 3 monthsParticipants who are judged by investigators to be unsuitable for participation in the clinical trial for other reasons

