### Early termination and dropout criteria

The criteria for early termination and dropout of individual participants are when the participants withdraw consent, request a discontinuation of the clinical trial, or violate the test plan. Based on the investigator’s judgment, participants will be removed from the study if they are no longer able to participate in the trial due to adverse reactions or concomitant disease or if they take prohibited drugs that can affect the outcome of the study. In addition, if it is judged that the efficacy evaluation is not suitable because the compliance rate with the investigational drug is less than 70%, or if the participants cannot be tracked, treatment will be discontinued early. If moderate or severe adverse reactions judged to be related to the clinical trial occur in more than 25% of the total participants, or if the required number of participants has not been enrolled despite a sufficient recruitment period, this clinical trial may be terminated early.

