### Sample size

This is the first study to explore the feasibility and lipid-improving effect and safety of HHT granules compared with placebo granules. Therefore, a formal sample size calculation is not required [26]. Based on a study recommending a minimum of 12 participants per group for a pilot study [27], we selected 15 participants per group as a sample size for this trial, considering a 20% dropout rate.

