### Statistical analysis

An independent statistician will conduct statistical analysis using SAS® Version 9.4 (SAS Institute Inc., Cary, NC). In principle, efficacy analysis will be conducted using a full analysis set according to the intention-to-treatment principle, including all randomly assigned participants receiving at least one evaluation after the investigational product has been prescribed at least once. If necessary, per protocol set (PPS) analysis will also be conducted including only participants who have completed the entire process as described in the protocol and have no significant violations. Participants less than 70% compliant with the investigational product will be excluded from the PPS analysis. Safety analysis will include all data obtained from participants who have taken at least one investigational product.

The demographic and general clinical characteristics of participants will be summarized by group. Continuous data will be presented as mean and 95% confidence intervals or median according to the distribution of the data and dichotomous data as frequency and percentage. Continuous data will be analyzed using the independent *t* test or Wilcoxon rank sum test, and dichotomous data will be analyzed using the chi-square test or Fisher’s exact test.

The primary outcome in this study is the mean change in LDL-C from baseline to week 8. A two-sided test with a significance level of 5% will be performed using an analysis of covariance with baseline as the covariate and the treatment group as the fixed factors. The intra-group changes of outcome measures from baseline to post-treatment will be analyzed using paired *t* test or Wilcoxon signed rank test for continuous variables and the chi-square test or Fisher’s exact test for dichotomous variables. Furthermore, repeated measures analysis of variance will be used to compare the differences in trends between visits in each group. Missing values will be replaced with the multiple imputation method. If necessary, a subgroup analysis can be performed by categorizing the participant’s initial characteristics at the screening or baseline visit.

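### Thyroid drugs are forbidden on study but missing from the entry drug list, so a person controlled on thyroxine meets every explicit criterion and then holds a forbidden drug

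*Protocol article*

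**What the plan says.** Four parts of the protocol article bear on this.

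- **Exclusion criteria.** Use of a list of lipid-active drugs is excluded with a look-back. The list ends with "systemic steroids, diuretics, amiodarone, and cyclosporin, which can affect the lipid profile within 4 weeks prior to screening". No thyroid drug is on it. Thyroid disease enters only through a separate criterion for uncontrolled function, set at TSH of 1.5 times the upper limit of normal or more. The last criterion lets the investigator exclude anyone judged unsuitable for other reasons.
- **Interventions.** The same lipid-active drugs, with the same omega-3 and short-course corticosteroid exceptions, are forbidden on study. One class is then added: "the use of drugs that can affect thyroid function such as thyroxine will be forbidden during the study period". No exception is given for stable prior use. Earlier in the section, "Co-administration of medications that are being used for the management of metabolic diseases, such as hypertension and diabetes" is permitted, along with certain supplements, and "participants will be instructed not to change the dose or type of concomitant medications as much as possible".
- **Early termination and dropout criteria.** Participants may be removed, on the investigator's judgement, "if they take prohibited drugs that can affect the outcome of the study".
- **Statistical analysis.** The full analysis set takes randomised participants with at least one evaluation after the product was prescribed. The per protocol set, run if necessary, takes those who "completed the entire process as described in the protocol and have no significant violations".

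**The concern.** Every other class in the on-study ban is screened for at entry by an explicit rule. Thyroid drugs are not. The thyroid criterion is worded like its neighbours for hypertension and diabetes, which exclude only the uncontrolled form. The plain reading is that controlled thyroid disease is eligible, including disease controlled by a drug that the protocol forbids once the study begins.

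The primary outcome is the change in LDL-C from baseline to week 8. By excluding uncontrolled thyroid function and banning thyroid drugs, the protocol shows that it regards thyroid status as something to be held steady. A participant who stops a maintenance drug to comply may have a change in thyroid status inside that window. A participant who continues is in breach from the first day, for a reason already visible at screening, where medication and concomitant disease are recorded.

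**Working it through.** **Step 1. The two drug lists side by side.**

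| Item | Entry (4 weeks before screening) | On-study ban |
|---|---|---|
| Statins, ezetimibe, fibrates, PCSK9 inhibitors, cholestyramine, nicotinic acid, omega-3 | excluded | forbidden |
| Systemic steroids, diuretics, amiodarone, cyclosporin | excluded | forbidden |
| Low-dose omega-3 and short-course corticosteroid exceptions | allowed | allowed |
| Drugs affecting thyroid function, thyroxine named | not listed | forbidden |

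The last row is the only one where the lists differ.

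**Step 2. A person on stable thyroxine with TSH below 1.5 times the upper limit.** Assume all other criteria are met. The TSH criterion does not exclude this person, and neither does the drug look-back. Only the unsuitability clause can, and it does not mention thyroid drugs.

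**Step 3. What follows if that person is randomised.**

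- *The drug is stopped.* The ban is obeyed, but thyroid status may change during the 8 weeks over which the primary outcome is measured. The documents give no size for any effect on LDL-C, and none is assumed here.
- *The drug is continued.* The ban is breached. If the investigator keeps the person in, week-8 LDL-C can be measured and the person stays in the full analysis set. Loss from the per protocol set follows if the breach is judged significant. If the investigator removes the person before week 8, the week-8 value is missing and falls to the planned multiple imputation.

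**Step 4. Scale.** The Sample size section gives a minimum of 12 per group and states that "we selected 15 participants per group as a sample size for this trial, considering a 20% dropout rate". That figure reproduces:

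12 / (1 − 0.20) = 15 per group.

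Places above the minimum: 15 − 12 = 3 per arm. One loss is 1/15 = 6.7% of an arm and 1/3 of those places.

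**Step 5. How often, under assumption only.** The documents give no prevalence of thyroxine use. Let p be the assumed proportion among people who would otherwise be randomised, with no use of the unsuitability clause. Among 30 participants the expected number is 30p, and the chance of at least one is 1 − (1 − p)^30.

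| Assumed p | Expected among 30 | Chance of at least one |
|---|---|---|
| 1% | 0.3 | 26% |
| 2% | 0.6 | 46% |
| 3% | 0.9 | 60% |
| 5% | 1.5 | 79% |

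Any use of the unsuitability clause lowers these figures.

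**The case against.** A reader might infer that the sections contradict each other outright and cannot all be followed. The documents do not support that. Medication is recorded at screening, randomisation comes later at the baseline visit, and an investigator who uses the unsuitability clause for a thyroxine user complies with every section. What remains is that this class alone depends on discretion where the others have an explicit rule.

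A reader might also see a conflict with the instruction to keep concomitant medication unchanged. That instruction is softened by its own wording and follows the text on permitted drugs, so it does not compete with a specific ban. The protocol also writes a continuation rule where it wants one, for existing users of lactic acid bacteria, and writes none for thyroxine. This suggests that thyroxine users were not meant to be on study, but the eligibility criteria do not say so.

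Nor do the documents support the reading that such a participant's week-8 LDL-C is bound to be disturbed or lost. The clause on prohibited drugs makes removal a matter of judgement and covers drugs that can affect the outcome. A participant on an unchanged dose can be measured and analysed in the full analysis set. No section says that maintenance treatment would be stopped at randomisation; that is one branch of two.

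Finally, several such participants in one arm can be imagined, but no prevalence in the documents stands behind that scenario. The 3 places are slack above a pilot minimum and do not come from a power calculation.

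These points limit the consequence. They do not close the gap between the two lists.

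**Conclusion.** The point holds as a mismatch between entry and conduct rules. Following the explicit criteria as printed can admit a participant who must then either stop a maintenance drug or breach the plan during the LDL-C measurement window. The unsuitability clause offers a way out, but it is discretionary and silent on thyroid drugs.

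The expected size is small. Under assumed prevalences of 1% to 5%, between 0.3 and 1.5 participants among 30 would be affected before any screening judgement. The most likely analysis cost is to the per protocol set, with the full analysis set touched only if a participant is removed early or thyroid status shifts. The conclusion rests on the text of the article alone and needs none of the assumed prevalences. It is worth correcting because the article prints the eligibility, prohibition and dropout rules itself, and because the trial is meant to test a design for a later confirmatory study, into which the mismatch could be carried.

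**What to change.** Reconcile the exclusion criteria, the prohibited-drug text under Interventions and the prohibited-drug clause under Early termination and dropout criteria, so that the entry list and the on-study list treat thyroid drugs identically. One shared list, cited in both places with its look-back, would do this. How thyroid drugs are handled in that list is for the clinical team to decide; no clinical rule is proposed here.

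The cost is a short wording change. Under Ethics and dissemination, any modification needs IRB re-approval before use and documentation in the trial registry, so there is some administrative work as well. Depending on the clinical team's decision, the recruitment pool may become slightly narrower. The Trial status section says recruitment had not started, which is the cheapest time to make the change.

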### Early termination and dropout criteria

The criteria for early termination and dropout of individual participants are when the participants withdraw consent, request a discontinuation of the clinical trial, or violate the test plan. Based on the investigator’s judgment, participants will be removed from the study if they are no longer able to participate in the trial due to adverse reactions or concomitant disease or if they take prohibited drugs that can affect the outcome of the study. In addition, if it is judged that the efficacy evaluation is not suitable because the compliance rate with the investigational drug is less than 70%, or if the participants cannot be tracked, treatment will be discontinued early. If moderate or severe adverse reactions judged to be related to the clinical trial occur in more than 25% of the total participants, or if the required number of participants has not been enrolled despite a sufficient recruitment period, this clinical trial may be terminated early.

### Data collection

#### Background information

Investigators will collect the demographic and clinical information of participants and perform vital sign measurement and laboratory tests only for those participants who voluntarily sign the informed consent form at the screening visit. Demographic data include age, gender, height, weight, smoking history, and alcohol consumption. General clinical information includes medical history, treatment history, concomitant disease, and medication. The personal information of the participants will be de-identified by using a coded ID number and will be stored securely at the institution to protect confidentiality and ensure access is limited to the investigators involved in the study.

### Efficacy outcomes

The primary outcome is the blood level of LDL-C, which will be measured at baseline and 4, 8, and 12 weeks after randomization. In this study, the primary endpoint is 8 weeks post-treatment. The secondary outcomes are other blood lipid parameters including TC, TG, HDL-C, non-HDL-C, non-HDL-C/HDL-C, apolipoprotein (Apo) A1, Apo B, Apo B/Apo A1, lipoprotein (a), and atherogenic index of plasma (Log(TG/HDL-C), and atherosclerosis biomarkers including high-sensitivity C-reactive protein (hs-CRP), fibrinogen, and homocysteine, which will be measured at baseline and 4, 8, and 12 weeks after randomization. Using VP-1000plus (OMRON Healthcare Co., Kyoto, Japan), the degree of vessel hardening will be assessed through brachial-ankle pulse wave velocity (baPWV). The degree of narrowing due to vascular lesions will be assessed by measuring the blood pressure difference between the ankle and arm using the ankle-brachial index (ABI) to determine the degree of arteriosclerosis. Blood glucose parameters including fasting glucose and HbA1c, blood pressure, and anthropometric parameters including body weight, body fat percentage, body fat mass, skeletal muscle mass, waist circumference, hip circumference, and waist-to-hip ratio will also be measured. The health-related quality of life before and after taking the investigational product will be measured using the five-level EuroQol-5 dimensions (EQ-5D-5L). The EQ-5D-5L is composed of 25 items in five domains including mobility, self-care, usual activities, pain/discomfort, and anxiety/depression. Participants will respond to each item with five response levels: no problems (level 1), slight, moderate, severe, and extreme problems (level 5) [23]. The Korean version of EQ-5D–5 L will be used after permission from the EuroQol Research Foundation. Blood lipid parameters, atherosclerosis biomarkers, the degree of arteriosclerosis, blood glucose parameters, blood pressure, anthropometric parameters, and EQ-5D-5L will be measured at baseline and 4, 8, and 12 weeks after randomization.

The changes in the cold and hot patterns for participants will be measured using a cold-heat pattern identification questionnaire at baseline and 8 weeks post-treatment. The cold-heat pattern identification questionnaire was developed by the Korea Institute of Oriental Medicine (KIOM) and is a self-report questionnaire consisting of eight items related to cold patterns and seven items related to hot patterns [24]. The reliability and validity of the questionnaire have been confirmed [25]. As an exploratory outcome measure, fecal samples of participants before and after taking the investigational product (baseline and 8 weeks post-treatment) will be examined to identify changes in the gut microbiome through next-generation sequencing. The time points for each outcome measure are presented in detail in Table 1.

